### Sample size estimates

2.11

Referring to aforementioned our preliminary study performed at the NCVC between July 2020 and March 2022, we observed an intergroup difference in the total ADAS-Cog scores of −2.35 with a standard deviation calculated from the pooled variance estimates of 3.86. In line with previous studies (30–32), the effect size, calculated as | − 2.35/3.86|, was deemed sufficient to detect a clinically meaningful difference. Consequently, the sample size calculation for testing the hypothesis of the superiority of resveratrol treatment over nontreatment, with a certain degree of power, was conducted.

Since the total ADAS-Cog score at baseline is expected to correlate with the change in total score, between-group comparisons will be made via the analysis of covariance using the total ADAS-Cog score at baseline as the covariate when analyzing the primary endpoint. Under this assumption, the minimum number is 45 subjects per group based on the number of subjects required for a two-sided significance level of 5% and 80% power. However, since point estimates of correlation coefficients assessed by the limited available data are difficult to refer to, we conservatively assumed that there was no correlation.

Considering the basis for the above calculation and the difference between the dose in the resveratrol group in the REVAMP trial and the dose in the resveratrol group in the preliminary study, the actual power in the REVAMP trial is expected to be sufficiently higher than assumed. Therefore, we will recruit 100 patients (50 patients per group), considering a dropout rate of 10%. A press release notifying about start of the REVAMP trial at NCVC was issued on the website of NCVC to reach the target sample size.

### Data collection

2.12

Web-based electronic data capture system with secure and restricted access will be used to collect clinical data obtained from patient medical records. Geographic data, medical history, medication information, laboratory data, and findings of neuropsychological tests and carotid ultrasonography will be stored in the system. Data will only be de-identified for analysis after this study. Shido Co., Ltd., a contract research organization, assigned to data management will perform quality control at each step of data handling to ensure the reliability of all data related to the trial, and maintain the web-based electronic data capture system.

### Data monitoring

2.13

The individuals assigned to data monitoring will be responsible for safeguarding the interests of trial participants, evaluating the safety and efficacy of the interventions throughout the trial, and monitoring the overall conduct of the trial. A formal data monitoring committee will not be set up because (a) it is known that long-term resveratrol administration has minimal risks (19, 20); (b) asymptomatic CASO is not a life-threatening disease; (c) interim analysis will not be planned; and (d) vulnerable participants such as pediatric patients, patients with severe mental retardation and severely demented patients who fail to undergo neuropsychological examinations will not be included.

### Statistical analysis

2.14

We will analyze a full analysis set (FAS), which is defined as data obtained from registered patients who will receive at least some of the assigned treatment and complete at least one assessment at the end of the 35 weeks. However, patients found to be ineligible after the registration will be excluded from the full analysis set. For the primary objective, the changes in total ADAS-Cog scores from the baseline to 35 weeks after starting protocol treatment will be tested using the analysis of covariance with covariates including the baseline ADAS-Cog total score, the existence of left CASO, and sex to assess the improvement in cognitive function brought about by the treatments In addition, the same analysis will be also performed on the per protocol set (PPS) as a supplementary analysis to confirm the robustness of the main analysis using the FAS. The PPS will not include the following categories of participants: (a) patients who will receive the prohibited concomitant care and interventions as outlined in the section 2.8 Intervention; (b) patients who will not attend visits at 35 weeks within the specified allowance; and (c) less than 75% of medication adherence. The REVAMP trial will judge the efficacy of resveratrol using these analyses. Changes in CBF, CMRO_2_, and OEF assessed by ^15^O–gas PET, white matter volume on brain magnetic resonance imaging and blood pressure from the baseline to 35 weeks will be also analyzed with the same procedure as the primary objective.

Changes from the baseline within a group will be analyzed using paired *t*-test or Wilcoxon signed-rank test, taking into account the data distribution, which Shapiro–Wilk test will be used to assess. Regarding other evaluation items, for continuous variables, the changes from baseline at each follow-up point will be evaluated using either paired *t*-test or Wilcoxon signed-rank test based on the data distribution. Comparisons do not take multiplicity into account. Student’s *t*-test or Wilcoxon rank-sum test will be used to evaluate the difference between the two groups based on the data distribution. For categorical variables, Fisher’s exact or χ^2^ test will be used. All reported *p*-values will be two-tailed, and *p* < 0.05 will be considered statistically significant.

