Before the start of the REsveratrol for VAscular cognitive impairment investigating cerebral Metabolism and Perfusion (REVAMP) trial, our preliminary retrospective observational study was conducted between July 2020 and March 2022 at the National Cerebral and Cardiovascular Center (NCVC) in Japan. The study involved 38 patients with asymptomatic CASO in the resveratrol-treated group and 44 patients with asymptomatic CASO in the nonresveratrol-treated group who underwent neuropsychological tests, such as the Alzheimer’s Disease Assessment Scale–cognitive subscale 13 (ADAS-Cog) (approval number of NCVC Research Ethics Committee: R20113). The mean observational period for the resveratrol-treated and nonresveratrol-treated groups was 223 ± 65 and 246 ± 87 days, respectively. We observed a significantly improved total ADAS-Cog score in the resveratrol group (−0.77 ± 1.88, 0.55 ± 1.74; *p* = 0.006) and an intergroup difference in the total ADAS-Cog scores of −2.35, calculated from the pooled variance estimates standard deviation of 3.86. Among the 82 patients, 79 underwent neuropsychological tests, such as ADAS-Cog and Montreal Cognitive Assessment (MoCA) and ^15^O-gas positron emission tomography (PET); 36 received resveratrol and 43 did not. Long-term resveratrol treatment significantly improved the memory domain and total score in the ADAS-Cog and the visuospatial/executive function in the MoCA. Furthermore, CBF improved in the anterior circulation territory and thalamus. No adverse events were observed (21).

Therefore, we hypothesized that long-term intake of resveratrol yielded beneficial effects on cognitive improvement accompanied by enhanced cerebral blood flow via pleiotropic effects such as activation of NAD^+^/SIRT1/eNOS axis, and decrease of oxidative stress and inflammation in patients with asymptomatic CASO. We aimed to prospectively determine whether the long-term clinical application of resveratrol at a daily dose of 150 mg improves cognitive impairment and the cerebral hemodynamic state, as assessed by ^15^O-gas PET, in patients with asymptomatic CASO. Herein, we provide a comprehensive description of the protocol for a clinical trial aimed at assessing the safety and efficacy of resveratrol administered at a daily dosage of 150 mg for patients with asymptomatic CASO.

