### Study objectives

2.2

The primary objective will be change of ADAS-Cog total score from baseline to assess the effectiveness of resveratrol in preserving or improving cognitive function in patients with asymptomatic CASO. The principal secondary objectives will be to evaluate the impact of resveratrol on the following: (i) the preservation or enhancement of cognitive function, as evaluated by a change in the total MoCA score and the trail-making test score from baseline; (ii) the preservation or improvement of cerebral hemodynamic parameters, including CBF, oxygen extraction fraction (OEF), and cerebral metabolic rate of oxygen (CMRO_2_) as measured by ^15^O-gas PET (Table 1).

**Table 1 tab1:** Primary and secondary objectives.

Primary objective
Change of ADAS-Cog total score from baseline to 35 weeks.
Secondary objectives
1.Changes of MoCA total score and trail making test from baseline to 35 weeks. 2.Change of CBF examined by brain ^15^O gas-PET from baseline to 35 weeks. 3.Change of OEF examined by brain ^15^O gas-PET from baseline to 35 weeks. 4.Change of CMRO_2_ examined by brain ^15^O gas-PET from baseline to 35 weeks. 5.Volume or grade changes of white matter hyperintensities examined by brain magnetic resonance imaging (MRI) from baseline to 35 weeks. 6.Number changes of cerebral microbleeds examined by brain MRI from baseline to 35 weeks. 7.Change of systolic and diastolic blood pressure from baseline to 35 weeks.

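### Within-arm tests of change from baseline are planned at p<0.05 and not labelled descriptive; they test change over time, not the effect of resveratrol, and could support secondary claims of preservation

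*Protocol article*

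**What the plan says.** Section 2.14 (Statistical analysis) of the protocol article has two layers.

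- **Between arms.** The change in total ADAS-Cog "will be tested using the analysis of covariance with covariates including the baseline ADAS-Cog total score, the existence of left CASO, and sex". This is done in the full analysis set and repeated in the per protocol set. The next statement is "The REVAMP trial will judge the efficacy of resveratrol using these analyses". The same procedure is extended to the PET measures, white matter volume and blood pressure.
- **Within arms.** A new paragraph then says "Changes from the baseline within a group will be analyzed using paired *t*-test or Wilcoxon signed-rank test", with Shapiro–Wilk used to assess the distribution. For the remaining continuous items, "the changes from baseline at each follow-up point will be evaluated using either paired *t*-test or Wilcoxon signed-rank test based on the data distribution". A Student's t or rank-sum test between the two groups follows.

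Two sentences cover everything: "Comparisons do not take multiplicity into account", and "All reported *p*-values will be two-tailed, and *p* < 0.05 will be considered statistically significant". Neither separates within-arm from between-arm p-values.

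MoCA and the trail-making test are not on the list of outcomes that get the analysis of covariance. They therefore appear to fall under the remaining items, where the paired test is named first. Section 2.2 states the principal secondary aim as "to evaluate the impact of resveratrol on the following: (i) the preservation or enhancement of cognitive function", measured by change from baseline in these two instruments.

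**The concern.** The trial is randomized and placebo-controlled, and its question is what resveratrol does. The matching null is no difference between the arms. A paired test in one arm has another null: zero mean change over the 35 weeks. Disease progression, practice on a repeated cognitive test and regression to the mean can each make that null false with no drug effect.

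The wording of the objectives makes this more than a formality. If placebo worsens with p<0.05 and resveratrol does not, the pair of results looks like preservation, and section 2.14 would allow the placebo result to be called statistically significant. But a difference in significance between two arms is not a test of the difference between them. The Introduction shows how easily one-arm wording arises. It reports the preliminary study as "We observed a significantly improved total ADAS-Cog score in the resveratrol group (−0.77 ± 1.88, 0.55 ± 1.74; *p* = 0.006", which states the improvement for one group although both groups' figures follow.

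At stake are the statements on secondary cognitive outcomes and other supplementary items. This is separate from multiplicity: even a single within-arm test answers a different question from the one posed.

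**Working it through.** **Inputs**
- Two-sided significance level 0.05 (section 2.14).
- Minimum of 45 per group, 50 recruited, 10% dropout; planning difference −2.35 and SD 3.86 (section 2.11).
- Untreated patients in the preliminary study: ADAS-Cog change 0.55 ± 1.74, n = 44 (Introduction). I read this as mean change ± SD, with a positive change meaning worsening. It is the only drift figure in the document.

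**The plan's own figure.** For two means, n = 2(1.96 + 0.84)² × (3.86/2.35)², which rounds up to 43 per arm; the t-based value is 43.3, so 44. Both are within two patients of the stated 45, and 45/0.90 = 50. The sample size is for the between-arm comparison. The article gives no rejection rate for the within-arm tests.

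**Within-arm rejection when resveratrol does nothing.** Give both arms the same drift. The paired t statistic is then noncentral t with n − 1 degrees of freedom and noncentrality (drift/SD) × √n. With n = 45 and drift 0.55:
- SD 1.74: 0.55/1.74 × √45 = 2.12
- SD 3.86: 0.55/3.86 × √45 = 0.96

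With p the rejection rate per arm, and the arms independent, exactly one arm is significant with probability 2p(1 − p). Placebo alone is significant with probability p(1 − p).

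| Drift in both arms | SD | p per arm | Exactly one arm | Placebo only |
|---|---|---|---|---|
| 0 | any | 5.0% | 9.5% | 4.8% |
| 0.25 | 1.74 | 15.6% | 26.4% | 13.2% |
| 0.25 | 3.86 | 7.1% | 13.2% | 6.6% |
| 0.55 | 1.74 | 54.5% | 49.6% | 24.8% |
| 0.55 | 3.86 | 15.5% | 26.1% | 13.1% |

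With 50 per arm and drift 0.55, the per-arm rates are 59.1% (SD 1.74) and 16.7% (SD 3.86).

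**Between-arm test on the same data.** In 20,000 simulated trials with drift 0.55 and SD 1.74 in both arms of 45, an unadjusted t-test (standing in for the analysis of covariance) rejected in 5.0%.

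**Direction.** At drift 0.55 almost all within-arm rejections are toward worsening. Rejection toward improvement is below 0.01% at SD 1.74 and about 0.2% at SD 3.86. The pattern that could mislead is therefore placebo-only significance, not apparent improvement on resveratrol.

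**Why two SDs.** The preliminary change SDs of 1.88 and 1.74 pool to 1.81, while planning uses 3.86. The article does not reconcile them, so both are shown.

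**The case against.** The strongest reply is that section 2.14 already says how efficacy is judged. "The REVAMP trial will judge the efficacy of resveratrol using these analyses" comes directly after the full analysis set and per protocol set analyses of covariance and before the within-arm paragraph. The PET measures, white matter volume and blood pressure get the same between-arm model, and the other items get a between-group test as well. No sentence says that a within-arm result will support an efficacy claim. This stands: the within-arm tests are additional, and the type I error of the primary conclusion is intact.

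The size also needs care. A reader might infer that these tests reject in about half of trials whenever resveratrol does nothing. The document does not support that. The figure applies per arm, to ADAS-Cog, and only if the preliminary drift and its SD recur. That drift comes from untreated patients in a retrospective study and is imprecise: 0.55 ± 2.02 × 1.74/√44 gives a 95% interval of about 0.02 to 1.08. No drift is given for any other outcome, so no rate can be stated for MoCA, trail-making, PET, MRI or blood pressure.

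Nor is 55% a false-positive rate of the paired test. That test is right to reject when the mean change is not zero. The error arises only if the result is read as a treatment effect.

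The reply does not remove the point. The sentence on judging efficacy does not tell the reader how to treat the within-arm p-values, and the blanket significance sentence includes them.

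**Conclusion.** The point holds as a matter of labelling and reporting for secondary and supplementary results. Section 2.14 prescribes within-arm tests whose null is not the trial's question, applies the 0.05 threshold to them and does not call them descriptive. With objectives framed as preservation, a placebo-only significant result could be taken for a treatment effect.

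Its size is illustrated for ADAS-Cog only, assuming no drug effect, a common drift of +0.55, approximately normal changes and 45 evaluable patients per arm. The per-arm rejection rate is about 55% at SD 1.74 or 16% at SD 3.86, and the placebo-only split occurs in about 25% or 13%. With no drift, the per-arm rate is 5%.

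It would be wrong to infer that the primary efficacy conclusion is compromised or that the placebo arm goes unused. Severity is minor to moderate. The change is worth making because it is nearly free.

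**What to change.** In section 2.14, or in the statistical analysis plan before unblinding:

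1. Replace the two within-arm testing sentences with a statement that changes from baseline in each arm will be summarised descriptively (mean change with 95% CI, or median and interquartile range), without p-values.
2. State that every conclusion on the effect of resveratrol, including preservation, rests on the between-group difference in change with its 95% CI.
3. Limit the p<0.05 sentence to between-group comparisons.
4. Move the Shapiro–Wilk statement to the sentence on Student's t and rank-sum tests. It now sits in the within-arm sentence, and deleting it would leave the between-group choice of test without its stated criterion.

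The cost is a wording change and the loss of the within-arm p-values. The within-arm estimates and intervals stay, and no further patients or data are needed.

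### MoCA and trail-making, which are among the principal secondary endpoints, are left out of the ANCOVA and fall to an unadjusted test whose type depends on the observed data

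*Protocol article*

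**What the plan says.** Section 2.2 of the protocol article puts two groups under the principal secondary objectives. The first is cognition, "as evaluated by a change in the total MoCA score and the trail-making test score from baseline". The second is the PET measures CBF, OEF and CMRO2. Table 1 lists the cognitive pair as secondary objective 1: "Changes of MoCA total score and trail making test from baseline to 35 weeks".

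Section 2.14 tests the primary endpoint, change in ADAS-Cog, by ANCOVA with "covariates including the baseline ADAS-Cog total score, the existence of left CASO, and sex". It then says that changes in CBF, CMRO2, OEF, white matter volume and blood pressure "will be also analyzed with the same procedure as the primary objective". MoCA and trail-making are in neither sentence and are named nowhere in section 2.14.

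For remaining continuous items, the section gives paired tests within each group. Between groups it gives Student's t or the alternative: "Wilcoxon rank-sum test will be used to evaluate the difference between the two groups based on the data distribution". Shapiro–Wilk is named as the check of distribution, but only in the within-group sentence and with no threshold.

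Two other places bear on this. Section 2.7 minimizes on sex, left CASO and an ADAS-Cog total of 15 or more. Section 2.11 explains the primary ANCOVA by the expected correlation between baseline ADAS-Cog and its change.

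**The concern.** MoCA and trail-making are the two other cognitive measures in the trial, so they are the natural support for an ADAS-Cog result. Under the stated rule they get a weaker analysis than blood pressure, which is last in Table 1, and no reason is given.

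Three things follow:

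- The argument in section 2.11 for adjusting ADAS-Cog for its baseline applies equally to these two scores, but is not carried over.
- The factors used to balance the arms are left out of the comparison.
- A t-test goes with a mean difference and a rank-sum test with a comparison of ranks, so the effect to be reported is settled only when the data are looked at.

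There is a related uncertainty for the outcomes that do get the ANCOVA. The procedure being copied contains baseline ADAS-Cog. Taken literally, change in CBF or blood pressure would be adjusted for baseline ADAS-Cog and not for baseline CBF or blood pressure.

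**Working it through.** **The plan's own figure.** Section 2.11 gives a difference of −2.35, SD 3.86, two-sided 5%, 80% power and 45 per group. The normal approximation gives 2 × (1.960 + 0.842)² × (3.86/2.35)² = 42.4, so 43; the t-based calculation gives 44. The stated 45 is within two patients of both, and 45/0.9 = 50 matches the recruitment target. This point therefore touches no stated figure. I use 45 per group below.

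**Precision lost by not adjusting.** Let s be the SD of the score at each visit (assumed equal) and ρ the correlation between baseline and week 35.

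- Variance of the change score: 2s²(1 − ρ)
- Residual variance after ANCOVA on own baseline: s²(1 − ρ²)
- Ratio, ANCOVA to change: (1 − ρ)(1 + ρ) / [2(1 − ρ)] = (1 + ρ)/2

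The article gives no ρ for MoCA, trail-making, PET or blood pressure, so a range is shown. The last column takes an unadjusted test on change with 80% power as its starting point.

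| ρ (assumed) | Variance ratio | Extra patients needed without adjustment | What 45 per group is worth with ANCOVA | Power with ANCOVA |
|---|---|---|---|---|
| 0.5 | 0.75 | 1/0.75 − 1 = 33% | 60 | 90% |
| 0.7 | 0.85 | 1/0.85 − 1 = 18% | 53 | 86% |
| 0.8 | 0.90 | 1/0.90 − 1 = 11% | 50 | 84% |
| 0.9 | 0.95 | 1/0.95 − 1 = 5% | 47 | 82% |

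**Simulation.** This used 45 per arm, ρ of 0.5, 0.7 and 0.8, and an effect set to give the unadjusted test about 80% power. Errors were normal or log-normal. The gate was Shapiro–Wilk in each arm at 0.05, which is my choice because the article gives no threshold. There were 6,000 runs under no effect and 3,000 under the effect.

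- Type I error of the gated choice between t and rank-sum was 4.5% to 5.4% over all settings. There is no material inflation.
- With normal errors, power was 78–80% for the t-test and 82–89% for ANCOVA on own baseline.
- With normal errors, ANCOVA on a substitute covariate correlated 0.3 with own baseline gave 78–81%. A covariate only weakly related to the outcome's baseline, as baseline ADAS-Cog might be for CBF or blood pressure, gains almost nothing over no adjustment.
- With strongly skewed (log-normal) errors, the gated choice reached 93–98%, against 83–89% for ANCOVA on own baseline. The precision argument therefore holds for roughly normal data, not for every shape.

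**Wording of the MRI outcome.** Table 1, item 5, concerns the volume or grade of white matter hyperintensities. Section 2.14 speaks of white matter volume. These are literally different quantities and the two places need to agree.

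**The case against.** The strongest reply is that this is a condensed article, that covariates for each secondary outcome are usually left to the analysis plan, and that section 2.14 judges efficacy on ADAS-Cog alone. The reply on efficacy stands: the primary test and the sample size are untouched. The reply on condensing does not remove the point, because the article is not silent. It states a between-group rule, and that rule takes in MoCA and trail-making.

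The size also depends on ρ. Section 1 reports ADAS-Cog values with ± 1.88 and ± 1.74 beside a pooled SD of 3.86. If the first two are SDs of change (about 1.81) and the last is the SD of the score, which the text does not make clear, then ρ = 1 − 1.81²/(2 × 3.86²) ≈ 0.89. The unadjusted test would then need only about 6% more patients. That is ADAS-Cog and not MoCA, but it warns against leading with the low-correlation figure. The skewed-error result also shows that a rank test can be the more powerful one.

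A reader might infer more than the document supports:

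- *That MoCA and trail-making are the only principal secondary endpoints.* The PET measures have the same rank, and they do get the ANCOVA.
- *That baseline is not used at all.* The endpoint is change, so baseline enters by subtraction. What is missing is baseline as a covariate.
- *That the test is chosen after unblinding, or freely.* The article does not say when the distribution is checked, and it does name Shapiro–Wilk.
- *That false positives rise.* The simulation shows no such effect, and leaving out balancing factors generally makes a test slightly conservative.
- *That the PET and blood-pressure models certainly use baseline ADAS-Cog.* Given the reasoning in section 2.11, copying the procedure can equally mean each outcome's own baseline.
- *That an MRI objective would be tested on the wrong variable.* No other white matter objective exists, so the phrase is probably shorthand.

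**Conclusion.** The point holds for MoCA and trail-making. As written, they are compared between groups on change by an unadjusted t or rank-sum test picked from the observed distribution. This does not fit the protocol's own reason for baseline adjustment, and it leaves the effect measure unfixed until the data are seen.

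The harm is modest: a 5% to 25% variance reduction is forgone for ρ from 0.9 to 0.5, or about 2 to 10 power points from a base of 80%. This rests on an assumed ρ, equal SDs at both visits and roughly normal data. The unfixed effect measure does not depend on those assumptions.

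For the PET, MRI and blood-pressure outcomes the finding is an ambiguity about the baseline covariate, not an established error. The white matter wording is a mismatch to be aligned. None of this affects the primary analysis. It should still be corrected, because these endpoints will be read alongside the primary result.

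**What to change.** In section 2.14, and in the analysis plan:

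1. Name MoCA and trail-making in the sentence that extends the ANCOVA to secondary outcomes.
2. State that each continuous secondary outcome is adjusted for its own baseline value plus the minimization factors: sex, left CASO and baseline ADAS-Cog.
3. Make this the fixed between-group analysis in place of the distribution-dependent choice. If a rank-based analysis is wanted, for example because skewness is expected, prespecify it as a sensitivity analysis.
4. Align white matter volume in section 2.14 with the white matter hyperintensity objective in Table 1.

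Whether to transform trail-making scores or use robust standard errors is a matter of preference for the analysis plan and is not needed to settle this point.

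The cost is wording only. Section 2.5 already collects MoCA, trail-making, ADAS-Cog, PET and MRI at baseline, and section 2.4 collects vital signs at screening. No visit, measurement or patient is added.
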